##### BV and GBS

All swabs and blood samples are processed using standard laboratory practices by accredited medical laboratories in the study centres. Vaginal swabs for BV and vagino-rectal swabs for GBS are self-collected by woman at enrolment (baseline) and 35–37 weeks gestation (outcome) following standardised written instructions and using Copan Transystem Amies (Ref 108CF.FR) swabs. Additional file 1: Figure S1 shows the swab collection instructions in more detail. After collection, swabs are transported at ambient temperature to laboratories as soon as is possible but within a maximum of 24 h. BV swabs are gram stained, and reported according to the three bands of Nugent’s scale, (0–3 being normal, 4–6 intermediate, and 7 or more indicating BV) [70]. GBS swabs are reported according to the presence or absence of GBS. As GBS is not treated in early pregnancy and BV is only treated if symptomatic, the results of baseline swabs remain confidential to the study. This is to ensure study swabs do not unintentionally result in unrequired antibiotic treatment being prescribed by reporting positive swabs which may not be from symptomatic disease. Only the results of the outcome 35–37 week GBS swabs are shared with the woman’s lead maternity carer (LMC)^1^ as these swabs inform the woman’s clinical care.

##### Maternal postpartum depression and anxiety

At 12 months post birth or later women will be asked to provide retrospective information related to their mood at 1–2 months after birth. Questions include the EPDS [71], state anxiety inventory [72], with the addition of questions to collect medication use for emotional and psychological problems.

#### Other measures

##### Anthropometric measures

Anthropometric measures are being performed using regularly calibrated standardised equipment and according to protocols adapted from the World Health Organisation [73] (see Additional file 2: Table S3).

##### Food diaries and faecal samples

Three day food diaries and faecal samples are collected from women at the time of their OGTT, and infants at 12 months. Participants are requested to prospectively record all foods and drinks taken during the diary period including the amounts taken, methods of cooking, any additions to the food (e.g. sauces) and any dietary supplements taken during the period. The food dairy is completed in the 2–3 days immediately prior to the collection of a faecal sample.

Faecal samples are collected into clean containers, then a small portion of faecal material is immediately transferred into hospital grade faecal sample pots and frozen at −20 °C with the sample container surrounded by water to ensure the sample remains frozen while being transferred to the research centre. Samples are collected no more than 48 h before being transferred to the research centres and stored at −80 °C. A range of quality control data are collected regarding these samples, detailed in Additional file 3: Table S4.

##### Cord blood and tissue samples

Cord blood and cord tissue samples are collected from participants in Wellington only. These samples are being collected for a range of studies to elucidate the mechanisms of probiotic action including cytokine, epigenetic and metabolomic studies (see Table 1). Using standardised instructions, intra-partum carers collect up to 40 ml of cord blood using an 18 gauge needle and sterile syringe, and 2 cord tissue samples. Further details of sample collection, processing and quality control data are presented in Additional file 4: Table S5.

##### Breast milk samples

Pre-feed breast milk samples are collected by women at 4–7 days after birth after the breast milk has come in. Women are advised to wash their hands prior to sample collection, then express a few drops of milk and discard before expressing a 10–15 ml into a sterile polypropylene 70 ml container. This sample is divided between three 5 ml sterile leak-proof freestanding polypropylene polyethylene Rnase and Dnase free tubes (Interlab code 3811-345-008). Samples are chilled in the home refrigerator if the sample will be picked up by research staff within 48 h or frozen in the home freezer with water surrounding the milk tubes if the sample will be picked up more than 48 h after collection [74]. All samples are stored at −80 °C. Quality data collected for these samples are documented in Additional file 5: Table S6.

##### Infant skin swabs

To enable examination of the infant skin microbiota two skin swabs are taken, one from the infants left neck (a common site for eczema) and another from the left axilla (a site where eczema is uncommon) at the 12 month visit using protocols adapted from the manual of procedures from the Human Microbiome Project [75]. Prior to sampling, parents are advised to avoid the following: antibiotic or steroid creams for 7 days (if possible), antiseptic or antimicrobial soaps or bath additives for 48 h, swimming for 48 h, washing for 24 h, and any creams or oils on the skin on the day of the visit. Questionnaire data is obtained to assess compliance with these preparations and to collect data related to any antibiotic use which may alter swab outcomes. To avoid possible contamination of samples with the researcher’s skin microbiota, these samples are collected at the commencement of the study visit and prior to the researcher having other physical contact with the infant. Samples are collected using sterile gloves and aseptic technique and Eswabs containing Amies fluid (480CE ESwab LQ Amies Reg. Nylon Flocked Applicator, Copan). Neck swabs are taken from the left side of the neck midway down a vertical line from earlobe to base of neck. The swab is moistened in Amies fluid and then using firm pressure and covering an area of 4 cm^2^ swabbed back and forth five times (one complete swab of back and forth is counted as one cycle). The swab is then rotated so the opposite swab surface is touching child’s skin and rubbed back and forth again in the same area for a further five cycles. A second swab is taken from the left axilla in the same manner. Following collection, swabs are immediately placed on ice prior to storage at −80 °C. Quality data includes date and time of swab collection and placement at −80 °C, and if full 10 cycles of swabbing is completed.

##### Infant buccal sample

Two infant buccal samples are taken at 12 months to enable future genotyping and epigenetic analysis. To prevent sample contamination parents are advised to avoid giving their child anything other than water to eat or drink, and to avoid cleaning teeth in the hour prior to sample collection. Research staff wear clean gloves and samples are collected using sterile Copan 502CS01 regular flocked swabs and by rubbing up and down 10 times against the inside of the cheek then gently rubbing in the grooves next to the top and bottom gums on the same side for 10 s. Swabs are placed in sterile 5 ml sterile SIMP309-5A cryovials and immediately placed on ice until transferred to a −80 °C freezer. Date and time of swab collection and time of placement at −80 °C are recorded. The child’s grandparents and mother’s ethnicity are recorded.

### Safety and adverse event monitoring

Our previous study using HN001 in women from 35 weeks gestation until 6 months post birth and in their infants for 2 years found no adverse effects [76]. Similarly other studies of safety using differing strains of *Lactobacillus rhamnosus* [77], and studies with interventions commencing from the first trimester [31, 78] have found no adverse effects on maternal (gestation length, miscarriage, caesarean delivery) or infant (Apgar score, birth weight and length, head circumference) outcomes.

Adverse event data are collected in all questionnaires. In addition, study doctors review the notes of any participant where there is any event that may require review, such as if the infant is delivered at less than 37 weeks’ gestation; if an infant requires resuscitation at birth; if the infant has any malformations (apart from tongue tie); if the infant requires admission to neonatal unit for more than 48 h for any reason; if the woman or baby had any hospital admission other than the birth admission; if the women or infant have any serious infection (e.g. septicaemia) or any other serious health issues.

### Data analysis

An intention-to-treat analysis will be used to assess the effect of HN001 on the 12 month cumulative prevalence of eczema and SCORAD ≥10 using hazard ratios from a Cox’s proportional hazards model, and the point prevalence of atopy at age 12 months using relative rates and a chi-squared test. Chi-square test will also be used to compare the proportion in each study group with detectable levels of immunological markers in breast milk and for those with detectable levels, t-tests will be used to compare the groups if the data is log-normally distributed. If the data is not log-normally distributed a Wilcoxon Rank-Sum test will be used. Where there are important differences between groups, these variables will be added to the models to assess whether these variables mediate any effect of HN001 on eczema and/or atopic sensitisation (using a generalised linear model with a log link and binomial distribution). The association of HN001 with the presence of GDM, BV and GBS will be assessed using relative rates and chi-squared tests. EPDS and State Anxiety Inventory will be compared with a Wilcoxon Rank-Sum test. The effect of weight gain will be investigated as an intermediate variable by adding it to the model (a generalised linear model with a log link and binomial distribution) in the GDM analysis. Any baseline differences that occur will be adjusted for. If commercially available non-study probiotics have been used, a sub-group analysis will be performed after excluding this group, which we do not expect to be large. Reasons for withdrawal from the study will be recorded and examined for differences between study groups. Adjustment will be made for differences in antibiotic use between study groups. SAS version 9.4 will be used.

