**Methods/design:**

The PiP Study is a two-centre, randomised, double-blind placebo-controlled trial in Wellington and Auckland, New Zealand. Four hundred pregnant women expecting infants at high risk of allergic disease will be enrolled in the study at 14–16 weeks gestation and randomised to receive either *Lactobacillus rhamnosus* HN001 (6 × 10^9^ colony-forming units per day (cfu/day)) or placebo until delivery and then continuing until 6 months post-partum, if breastfeeding.

Primary infant outcomes are the development and severity of eczema and atopic sensitisation in the first year of life. Secondary outcomes are diagnosis of maternal gestational diabetes mellitus, presence of bacterial vaginosis and vaginal carriage of Group B Streptococcus (at 35–37 weeks gestation). Other outcome measures include maternal weight gain, maternal postpartum depression and anxiety, infant birth weight, preterm birth, and rate of caesarean sections. A range of samples including maternal and infant faecal samples, maternal blood samples, cord blood and infant cord tissue samples, breast milk, infant skin swabs and infant buccal swabs will be collected for the investigation of the mechanisms of probiotic action.

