#### Atopic sensitisation

In general, effects of probiotics on sensitisation have only been seen in a subset of children with allergic [16] or sensitised mothers [12]. Assuming 60 % of mothers are skin prick test positive and a reduction in the prevalence of atopy from 50 to 26 % among their children, as seen in the paper by Huurre et al. [12], with a sample size of 200 pregnant women (120 with mothers who are sensitised) in each group and 13 % drop-out rate our study will have 95 % power at the 5 % level of significance, for atopic sensitisation among the children of mothers that are skin prick test positive. A further analysis of the data from the study by Huurre et al. [12] shows that there is a four-fold increased risk of sensitisation in the sub-group without maternal sensitisation. Assuming a similar difference in risk dependent on mother’s atopic status, the study would have >99 % power to show an interaction effect.

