### Study assessments

Table 2 provides a summary of the study timeline and investigations. Women enrolled in the study are provided with a study calendar to assist them to prospectively record data relevant to the study questionnaires. Research staff members are trained in standardised administration of all study questionnaires and data collection procedures.

**Table 2 Tab2:** Study timeline and investigations

		14-16 Weeks Gestation	26-28 Weeks Gestation	35-37 Weeks Gestation	Birth	3-7 Days After Birth	Infant Age 3 Months	Infant Age 6 Months	Infant Age 12 Months
	Intervention: new bottle study capsules	✓ Intervention commences	✓			✓	✓	Intervention stops	
	Questionnaire	✓	✓			✓	✓	✓	✓
Objective measures and samples: Maternal									
	Vaginal swab (BV)	✓		✓					
	Vagino-rectal swab (GBS)	✓		✓					
	Anthropometry^a,b,c,d^	✓				✓		✓	✓
	Blood samples (OGTT and serum)		✓^e^						
	Faecal sample		✓						
	3 day food diary		✓						
	Cord blood and tissue				✓				
	Breast milk					✓			
	Skin prick test							✓Completed after birth	
Objective measures and samples: Infant									
	Anthropometry^a,b,c^					✓		✓	✓
	Eczema							✓	✓
	SCORAD							✓	✓
	Faecal sample								✓
	48 hour food diary								✓
	Buccal sample								✓
	Skin swabs								✓
	Skin prick test								✓
Objective measures and samples: Paternal									
	Anthropometry^a,b,c^					✓Completed at any visit after birth			
	Skin prick test					✓Completed at any visit after birth			

*BV* bacterial vaginosis, *GBS* group B streptococcus, *OGTT* oral glucose tolerance test, *SCORAD* scoring atopic dermatitis

^a^height/length ^b^weight ^c^head circumference ^d^waist circumference ^e^excluding women with pre-existing diabetes

Questionnaires collect a range of data including confounders (such as previous GDM, parity etc.), effect modifiers (such as use of antibiotics, yoghurt etc.), outcome data, and adverse events.

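### The power figures for atopic sensitisation belong to a maternal-sensitisation subgroup and an interaction, but the Data analysis section lists only an all-infant chi-squared test

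*Protocol article*

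**What the plan says.** The abstract of the protocol article makes sensitisation a primary outcome: "Primary infant outcomes are the development and severity of eczema and atopic sensitisation in the first year of life". It is the third primary outcome in Table 1, and the hypothesis under Study design and outcomes is stated for infants overall.

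The Atopic sensitisation part of the sample size section starts from "Assuming 60 % of mothers are skin prick test positive" and "a reduction in the prevalence of atopy from 50 to 26 % among their children". It plans "with a sample size of 200 pregnant women (120 with mothers who are sensitised) in each group and 13 % drop-out rate" and obtains 95% power at the 5% level, "for atopic sensitisation among the children of mothers that are skin prick test positive". It then reports, from a further analysis of the same earlier trial, that "there is a four-fold increased risk of sensitisation in the sub-group without maternal sensitisation". Assuming a similar contrast here, it gives more than 99% power for an interaction.

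The Data analysis section names, for this outcome, an intention-to-treat comparison of "the point prevalence of atopy at age 12 months using relative rates and a chi-squared test". The only subgroup analysis it names excludes users of non-study probiotics. Maternal sensitisation does not appear in it. Under Study population, all infants are eligible for the outcomes (first-born only in multiple births). Table 2 marks the maternal skin prick test "Completed after birth".

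**The concern.** The sample size section and the Data analysis section describe different analyses of the same primary outcome. One is powered within a maternal stratum and for a difference between strata. The other compares the two arms in all infants. If the effects run in opposite directions, as the interaction figure assumes, they offset each other in the pooled comparison.

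A non-significant all-infant result could then hide a fall from 50% to 26% in about 60% of infants and a rise in the other 40%. The Background says the trial may help to separate exactly these two groups. If the stratum and interaction analyses are run anyway, they will look post hoc, because the analysis section does not list them. A reader could also carry the 95% over to a test for which it was never calculated.

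**Working it through.** **Inputs from the sample size section.** 200 women per arm, 60% skin-prick positive, 13% drop-out, 5% level (two-sided assumed). Infants of sensitised mothers: 50% on placebo, 26% on HN001. Infants of non-sensitised mothers: four-fold increase.

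**Assumption.** The placebo risk p in infants of non-sensitised mothers is not given; 5% to 20% is shown. Four-fold is read as a risk ratio and, as a variant, as an odds ratio.

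**Evaluable infants per arm.** All: 200 × 0.87 = 174. Sensitised mothers: 120 × 0.87 = 104.4. Non-sensitised mothers: 80 × 0.87 = 69.6.

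**Formula.** For n per arm and risks a (placebo) and b (HN001), with m their mean:

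power for benefit = Φ{[(a − b)√n − 1.96√(2m(1 − m))] / √(a(1 − a) + b(1 − b))}

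**Reproducing the stated figure.** With n = 104.4, a = 0.50, b = 0.26: (0.24 × 10.218 − 1.96 × 0.686) / 0.665 = 1.66, so power is 95.2%. The stated 95% is right for that stratum.

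**The listed test, n = 174 per arm.**

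- Placebo risk in all infants: 0.6 × 0.50 + 0.4p = 0.30 + 0.4p.
- HN001 risk, risk-ratio reading: 0.6 × 0.26 + 0.4 × 4p = 0.156 + 1.6p.
- Difference: 0.144 − 1.2p, which is zero at p = 12%.
- HN001 risk, odds-ratio reading: 0.156 + 0.4q, where q has four times the odds of p.

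| p | Placebo, all infants | HN001 (risk × 4) | Power for benefit | HN001 (odds × 4) | Power for benefit |
|---|---|---|---|---|---|
| 5% | 32.0% | 23.6% | 42% | 22.6% | 51% |
| 8% | 33.2% | 28.4% | 16% | 25.9% | 32% |
| 10% | 34.0% | 31.6% | 7% | 27.9% | 23% |
| 12% | 34.8% | 34.8% | 2.5% (null) | 29.7% | 17% |
| 15% | 36.0% | 39.6% | 0.4% (reversed) | 32.2% | 11% |
| 20% | 38.0% | 47.6% | <0.1% (reversed) | 35.6% | 7% |

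At p = 20% on the risk-ratio reading, the test has 44% power in the direction of harm. Below the assumed range, at p = 2%, power for benefit is 74% to 75%.

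**Consistency with the interaction figure.** More than 99% interaction power itself limits p (Wald test, 104.4 and 69.6 per arm).

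- On the log-odds scale it needs p of about 7% or more (risk ratio) or about 10% or more (odds ratio). All-infant power for benefit is then at most about 25%.
- On the risk-difference scale it needs p of about 3.5% (risk ratio) or 4.5% (odds ratio) or more. The ceiling is then about 58% or 55%.

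**No effect in infants of non-sensitised mothers.** The difference is 0.6 × 0.24 = 14.4 points, and power is 82% to 89% for p from 2% to 25%.

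**The case against.** The sample size section makes no false claim. It ties the 95% to infants of skin-prick-positive mothers in the same sentence and attaches no power to an all-infant test. A reader might infer that the plan promises 95% for the all-infant comparison and delivers almost none of it; the text does not support that.

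A reader might also infer that the plan's own assumptions predict a near-null overall result. That needs the placebo risk in infants of non-sensitised mothers, which is not given. On the risk-ratio reading the expected overall relative rate runs from 0.74 at p = 5%, through 1.00 at 12%, to 1.25 at 20%, so near null is only one part of the range. The four-fold increase is also conditional: it is used only for the interaction power, and the Background calls the risk possible.

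An all-infant intention-to-treat test is legitimate. It matches the stated hypothesis, and the sponsor's earlier HN001 trial reported less sensitisation by 6 years in the whole HN001 group. Demoting it in favour of a modifier measured after birth would be debatable. These points stand, and they limit the conclusion.

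The remaining argument is that a journal article may leave the subgroup and interaction models to a fuller plan. Such a plan may well contain them. But the Data analysis section is specific: it sets out mediator models, a weight-gain model, antibiotic adjustment and one subgroup analysis. For this outcome it states a different analysis from the one that was powered. That is a mismatch within the article, not a detail left out.

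**Conclusion.** The point holds as a mismatch between two sections. Primary outcome 3 is powered for a stratum and an interaction, and the analysis section lists neither.

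Under the opposing effects assumed for the interaction, the listed test has power for benefit from about 51% down to under 1% for an assumed p of 5% to 20%. The overall effect is diluted, null or reversed depending on p. With no effect in the non-sensitised stratum, power is 82% to 89%. No scenario computed reaches 95% for benefit.

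This rests on the assumed p, on two-sided testing, on 13% drop-out applied equally to both strata, and on reading intention-to-treat plus the eligibility of all infants as an all-infant test. It does not show that the stated 95% is wrong or that a null overall result is to be expected.

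The timing of the maternal skin test is a lesser point. Done after birth, following months of capsules, it is a post-randomisation variable. The article gives no evidence that capsules alter it, so a check is enough.

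**What to change.** In Data analysis:

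- Prespecify the HN001 effect on sensitisation within each maternal skin-prick stratum, and the treatment-by-maternal-sensitisation interaction, from a log-binomial model. The section already uses this model type elsewhere.
- Keep the all-infant chi-squared test.
- State, before unblinding, which of these tests decides primary outcome 3.
- Compare maternal skin-prick positivity between arms, and repeat the stratified analysis with maternal allergic history recorded at enrolment as a sensitivity check. History is not the same as sensitisation, so this supports the main analysis and does not replace it.

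In the sample size section, give the power of the all-infant test together with the assumed placebo risk in infants of non-sensitised mothers, and the scale on which the interaction power was calculated.

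The cost is small. Maternal skin prick results are already being collected, and the article describes the trial as ongoing. There is a little more analysis, and the stated power for the all-infant test will look less favourable than the 95%.

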Almost without exception [12] previous probiotic trials of allergic disease with a pre-birth intervention have commenced at some time in the final 2 months of pregnancy [6]. In our current trial we commence the intervention from 14 to 16 weeks gestation and continue it throughout pregnancy and for 6 months post-partum while breastfeeding, the probiotic being only given to the mother, not directly to the infant. Our justification for an early probiotic intervention is based on evidence showing that fetal production of IgE antibodies occurs before the end of the first trimester and allergen-specific IgE antibodies towards the end of the second trimester [13]. There is also evidence that maternal allergy alters the regulation of antigen-specific responses during pregnancy, with non-allergic mothers showing down-regulation of their (already lower) Th2 responses to specific allergen from mid to late gestation [14]. This down-regulation was absent in allergic mothers. Epidemiological support for the importance of intervention in early pregnancy comes from a longitudinal study which shows that maternal exposure to pollen during the first trimester of pregnancy increased the risk of food sensitisation in the child [15]. The majority of probiotic trials, using a late pregnancy intervention (from 32 to 35 weeks gestation), may therefore have missed the critical window to influence fetal immune responses and thus the later development of allergic disease. This may explain the general lack of effect of probiotics on infant sensitisation. The only study, by Huurre et al. [12], that did show a protective effect of probiotics on sensitisation in the infant used an early pregnancy intervention and the effect was limited to those with sensitised mothers (OR = 0.34, 95 % CI 0.13–0.88). In that study [12], the group of infants with non-sensitised mothers had a significantly *increased* risk of sensitisation but this finding was not reported in the article.

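### The stated covariate rule for the mediation models follows between-arm imbalance, so a common cause of marker and outcome can make a marker that HN001 shifts look like a mediator

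*Protocol article*

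**What the plan says.** All of this stands in the protocol article, Data analysis section.

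- **Screen.** Breast-milk markers are first compared between arms: "Chi-square test will also be used to compare the proportion in each study group with detectable levels of immunological markers in breast milk", then by t-test or Wilcoxon test among detectable values.
- **Mediation step.** "Where there are important differences between groups, these variables will be added to the models", and the stated purpose is that "these variables will be added to the models to assess whether these variables mediate any effect of HN001 on eczema and/or atopic sensitisation". The model is fitted "using a generalised linear model with a log link and binomial distribution".
- **Same device for GDM.** "The effect of weight gain will be investigated as an intermediate variable by adding it to the model".
- **Covariates.** Two rules are given. One is "Any baseline differences that occur will be adjusted for". The other is "Adjustment will be made for differences in antibiotic use between study groups".

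The section on study assessments says that confounders such as previous GDM and parity are collected by questionnaire. Nothing ties them to the mediation models.

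**The concern.** Randomisation protects the comparison of HN001 with placebo on the marker and on the outcome. It does not protect the association between marker and outcome within arms, on which a mediation claim also depends. A factor that influences both creates such an association even when the marker does nothing.

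Arm imbalance is the wrong test for choosing covariates at this step. Randomisation tends to balance a common cause, so the stated rule will usually leave it out. Balance between arms does not stop it confounding marker with outcome.

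Maternal atopy is a plausible candidate. The background says that "maternal allergy alters the regulation of antigen-specific responses during pregnancy", and the sensitisation power calculation is built on maternal skin-prick status. The Clinical significance section hopes for insight into how the probiotic acts. At stake is that a correlate of maternal atopy is reported as the route by which HN001 works.

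**Working it through.** **Inputs from the article.** 200 per arm with 13% drop-out gives 200 × 0.87 = 174 per arm. Eczema: hazard ratio 0.39, 12.3% affected overall. Share of skin-prick positive mothers: 60%.

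**The plan's own figure.** Events: 400 × 0.87 × 0.123 = 42.8, so 43. Power: √43 × |ln 0.39| / 2 − 1.96 = 6.557 × 0.9416 / 2 − 1.96 = 1.13, and Φ(1.13) = 87%. This agrees with the article. It gives no figure for the mediation analysis.

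**Assumptions not in the documents.**
- Eczema: placebo risk 17.4%, risk ratio 0.41. This matches the article: (17.4 + 0.41 × 17.4) / 2 = 12.3%.
- Sensitisation: placebo risk 35%, risk ratio 0.70.
- HN001 shifts the marker by α = 0.5 residual SD in either direction.
- A common cause U (prevalence 60%) shifts the marker by δ = 0.5 or 1 SD and multiplies risk by 2 or 3.
- The marker has no effect on the outcome.

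**Expected bias.** With v = 0.6 × 0.4 = 0.24, omitting U gives the marker a spurious log-risk slope of about θ = ln(RR_U) × δv / (δ²v + 1). Adding the marker then changes the HN001 coefficient by −αθ.

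- δ = 0.5: δv / (δ²v + 1) = 0.12 / 1.06 = 0.113. For RR_U 2 and 3, θ = 0.078 and 0.124.
- δ = 1: 0.24 / 1.24 = 0.194. θ = 0.134 and 0.213.
- With α = −0.5 the HN001 coefficient moves towards the null by 0.5θ, that is 0.039 to 0.106.
- Relative to ln 0.41 = −0.892 this is about 4 to 12%. Relative to ln 0.70 = −0.357 it is about 11 to 30%.

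Simulated mean changes were slightly smaller, about 4 to 10% and 10 to 25%. With α = +0.5 the same quantity has the opposite sign and the HN001 effect looks stronger.

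**Simulated marker significance** (1,500 trials per scenario, marker entered after a 5% between-arm test; nominal level 5%):

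| U multiplies risk by | U shifts marker by | Eczema, without U | Eczema, with U | Sensitisation, without U | Sensitisation, with U |
|---|---|---|---|---|---|
| 2 | 0.5 SD | 8.4% | 5.3% | 14.2% | 4.1% |
| 2 | 1.0 SD | 15.4% | 5.6% | 39.1% | 5.2% |
| 3 | 0.5 SD | 11.8% | 4.4% | 24.7% | 5.6% |
| 3 | 1.0 SD | 29.3% | 5.5% | 68.0% | 6.5% |

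When U has no effect on risk the rate is 5 to 6%.

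**Significance together with attenuation.** This is the pattern that would be read as mediation of a protective effect.
- HN001 shift opposite to that of U: 9 to 30% (eczema), 15 to 69% (sensitisation).
- HN001 shift in the same direction as U: 0 to 1%.

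**The rule applied literally.** Suppose U is adjusted for only when the arms differ at p < 0.05. That happens in about 4 to 6% of trials. Marker significance is then still 9%, 17% and 33% for eczema and 16%, 36% and 62% for sensitisation (RR 2 with 0.5 SD, RR 2 with 1 SD, RR 3 with 1 SD).

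**Judging by change in the HN001 coefficient.** With placebo risk about 35%, risk ratio 0.6 and opposite signs, the coefficient moved more than 10% towards the null in 25 to 82% of runs without U and 10 to 15% with U. Two U settings here also used a risk ratio of 1.5 or 2 with a 0.5 SD shift. With no common cause the rate was 14%.

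**The case against.** Several points on the other side stand.

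- **The screen does real work.** Markers enter only after an important between-arm difference, so the HN001-to-marker path is checked too. A marker that HN001 does not move passes a 5% screen in only 4 to 5% of runs. A reader might infer that the plan tests nothing but marker-outcome association. It does more than that. But the screen gives no protection for markers that HN001 does move.
- **No decision rule is stated.** The article does not say that the marker's p-value settles mediation, and change in the HN001 coefficient is an equally natural reading. That reading is biased by the same omission.
- **Direction matters.** If HN001 and the common cause move the marker the same way, the HN001 effect strengthens on adjustment. Nobody would then call the marker a mediator of protection.
- **The confounder is plausible but not documented.** The background sentence concerns immune responses in pregnancy, and the power section uses maternal sensitisation as an effect modifier. Neither says that maternal allergy shifts a breast-milk marker, nor by how much it raises infant risk.
- **The full plan may say more.** The baseline-adjustment sentence is general, and an article commonly leaves covariate lists to the analysis plan. Silence alone would be no finding. Here, however, a criterion is stated, and it does not suit a mediation question.
- **The analysis is exploratory.** Breast-milk markers are related outcomes in Table 1.

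**Conclusion.** The point holds in limited form. Selecting covariates by between-arm difference does not control confounding of the mediator-outcome step, so a marker that HN001 shifts can be credited with mediation that it does not carry. A reader might infer that the plan will credit false mediators. The documents do not support that, because without a common cause marker significance stays near nominal and with shifts of the same sign the error takes another form.

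The ranges of 9 to 30% and 15 to 69% rest on assumed confounding strength, an assumed 0.5 SD shift by HN001 and opposite signs. At the weak end for eczema the excess is small. The upper ends need a 1 SD shift and tripled risk. The weight-gain model for GDM has the same structure, but its size was not computed. No primary or secondary treatment comparison is affected. The matter is worth correcting because the wrong conclusion would concern mechanism and the remedy is cheap.

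**What to change.** In the Data analysis section, state three things for the mediation models.

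1. They include a short pre-specified set of likely common causes of mediator and outcome, whether or not the arms differ on them. Examples for breast-milk markers are maternal allergic history and/or maternal skin-prick status, and parity. Examples for weight gain and GDM are previous GDM, parity and enrolment weight.
2. Mediation is judged by the estimated indirect effect with a confidence interval, with total and direct effects taken from models on the same log-risk scale.
3. The mediator-outcome step is reported as observational.

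No new data are needed. Allergic history is established for eligibility, questionnaires cover previous GDM and parity, and weight is measured at enrolment. Table 2 places the maternal skin prick test after birth, so using it assumes that HN001 does not alter it. The enrolment history avoids that assumption.

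The cost is a few extra terms. With HN001, the marker and three covariates, 43 eczema events give 43 / 5 = 8.6 events per term, so the list must stay short. The near-nominal rates above came from adjusting for the true common cause. Measured proxies may leave residual confounding, and the report should say so.
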